### Secondary outcome measures

The secondary endpoints in each of the three arms are: ICER at 24 months after the last rTMS or placebo session; the cost–utility ratio analysis over 12 and 24 months; 5-year budget impact analysis of the most efficient therapeutic strategies; and prognosis factors of maintenance after a response to an initial rTMS cure. Moreover, the following criteria will be compared between arms A and C, and between arms B and C: rates of responders; remission; disease-free survival at 12 and 24 months; depressive symptomatology evolution; tolerance; observance; treatment modifications; number of suicide attempts and suicide achieved; marital / professional status; and quality of life at 12 and 24 months.

### Statistical analysis

Descriptive analysis of the data collected during each patient evaluation will be carried up until the final evaluation. Specific time points for analysis in the three groups are: baseline; at 1 month after the last rTMS or sham sessions; and 12 and 24 months after the end of the first rTMS or sham course. Continuous variables will be described using median, standard deviation, minimal, maximal, and range for quantitative variables; qualitative variables will be described using frequencies and percentages. No data about quality of life, healthcare consumed, and the cost are available in the literature for this indication, making a priori the calculation of number of individuals needed impossible. The number of participants required for the present study was calculated according to the expected and sustained response in each arm (> 50% decrease in MADRS total score). This rate of responder after the rTMS cure is estimated at 60% in arms A and B at 1 year with 50% of success of rTMS [23, 48]. According to the literature, we hypothesized a rate of 30% maintained response at 1 year for arm A [23, 31, 49, 50] and arm B [23, 50–52], and 11% for arm C [53]. Assuming a 5% (bilateral) type I error, a power of 80%, and an attrition rate of 80%, a total of 318 individuals is required (106 in each arm). The study includes three arms, but only two comparisons will be carried out: arm A versus arm C, and arm B versus arm C.

For the ICER, resources consumed, including costs and QALY, will be presented with average and dispersion for each group. The comparison between cost, QALY, and the years of life gained in each arm, including ICER analysis, will be evaluated with the estimation of their standard deviation and their corresponding 95% confidence intervals (CI) following the non-parametric bootstrap method [54]. Tables will present differences between the three groups including their costs, QALY, and ICER. The ICER is calculated to consider the possibilities of vast dominance between these strategies [55]. For example, the ICER between arms A and C will be calculated as follows:

$$ ICER=\frac{C_{armA}-{C}_{armC}}{QALYs_{armA}-{QALYs}_{armC}} $$

*C*_*armA*_ and *C*_*armC*_ correspond to the costs of depression in each arm and are the QALYs’ gain associated with the rTMS maintenance versus usual cares without rTMS (placebo). At the end, a univariate and determinate sensibility analysis will be estimate with the Tornado method to evaluate the robustness of the resultants concerning the variation in the cost of rTMS sessions and the hypothesis of their pricing.

To estimate the costs of depression, clinical data matching the eCRF and the NHSD will be applied using the patient identification number. If there is a baseline deviation between arms of the study about the quality of life estimated with the EQ-5D, two analyses will be conducted: one with the quality of life raw score; and another with adjusted scores using a logistic regression model [56]. The cost–utility and EQ-5D analysis will be conducted according to the intent-to-treat (ITT) principle on two samples: one sample with completed cases including participants with completed data; and another with an imputed sample in which missing data about cost and quality of life will be imputed according a multiple imputation method.

The rate of remission with their corresponding 95% CIs at 12 and 24 months will be compared between arm A versus arm C, and arm B versus arm C according to the generalized linear model (logistic model) to consider the repeated measurements as a random factor (stratification factor of the randomization). Plots of relapse-free survival at 12 and 24 months will be estimated according to the Kaplan–Meier method; they will be compared between arms A and B, and between arms B and C using the Log-Rank stratified test in each center. A Cox multivariate analysis will be applied to evaluate the sustainability of the response in the time.

MADRS, MARS, CRS, and CGI scores with their corresponding 95% CIs will be compared between arms A and B, and between arms B and C according to a mixed logistic regression model to consider the center and repeated data as random factors. Modifications and side effects of pharmacological treatments will be described and compared using a Chi-squared test (or Fisher’s exact test, if appropriate). The number and percentage of suicidal attempts will be compared in the three arms using Fisher’s exact test. Marital status, professional status, and non-observance percentage (Maudsley Staging Model) will be described in the three arms at 12 and 24 months. The following criteria will be estimated for patients in each arm: responder and remission rate after rTMS or placebo cure; the number of cures prescribed; the duration of the rTMS cures and their side effects; observance rate; and the self-rated pain intensity of the procedure on a verbal analogue scale.

TMS indication is not yet approved in France. To evaluate its cost in the study in the French context, we used the cost-estimate of the rTMS cure calculated in France in 2015 [57]. According to this calculation, the hospital production cost of a rTMS session was estimated at 127.68 Euros (approximately US$141.64 calculated on Thursday, 22 August 2019, with 1 Euro = US$1.11) by session as detailed in Table 1.

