The gold-standard treatment of TRD is still electroconvulsive therapy (ECT), especially for depression with psychotic symptoms, severe resistance to pharmacological therapies, or life-threatening episodes, with a 48% response rate in ultra-resistant episodes [5, 15]. Repetitive transcranial magnetic stimulation (rTMS) is a non-invasive, focal and cortical stimulation technique enhancing neuronal plasticity throughout the modulation of cortical excitability [16]. This technique is an interesting alternative to ECT for resistant and middle to severe unipolar depression without psychotic symptoms [17], especially in conjunction with antidepressant chemotherapy [18, 19]. Two types of stimulations are widely applied – high frequency on the left dorsolateral prefrontal cortex (DLPFC) and low frequency on the right DLPFC – with evidence suggesting similar efficacy [20], and with the advantage for the 1 Hz protocol to be faster and better tolerated [21]. Since 2008, high frequency rTMS on the left DLPFC is validated in the United States by the Food and Drug Administration (FDA) to treat unipolar depression after the failure of one antidepressant treatment based on the study by O’Rearden et al. [22] involving 301 participants. Similar efficacy was shown among 170 patients with unipolar depression in France using low frequency rTMS on the right DLPFC [23]. In international guidelines, rTMS in the acute phase reached the best level of evidence (level 1) [17] after failure of one antidepressant. rTMS has the advantage of being somatic and cognitively well tolerated [24], without drug interaction [25], and improving the quality of life [26] with a huge rate of observance (an average rate of 3% for dropouts) [21].

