## Discussion

The study by Dunner et al. [53] evaluated the effects of TAU among 124 patients affected by a treatment-resistant, non-psychotic major depressive disorder or bipolar depression. They showed a response rate of 11.6% at 12 months and 18.4% at 24 months, with a 3.6% remission rate at 12 months and 7.8% at 24 months, and a poor quality of life globally. The Star*D study among 3671 participants retrieved results along these lines [7]. Indeed, only 20% were responders to an augmentation treatment after the failure of two treatments and 35% of them kept a 1-year profit. After a third treatment line, 28.5% were responders (59% of them were in remission). However, the recurrence rate at 1 year for remitted patients was 43%, and 76% for responders without remission. Pharmacological approaches actually rely on: posology optimization; switch (if inefficiency or intolerance); antidepressant association or potentiation with non-antidepressant treatments; and more or less adjuvant symptomatologic treatments [36, 58]. In addition to these strategies, rTMS may have the potential to improve treatment-resistant unipolar depression [59], with the advantages of being painless, well-tolerated, and twice as effective as placebo [60], even among elderly persons [61]. In a meta-analysis about rTMS efficacy, Kedzior et al. [51] demonstrated a significant decrease of depression scores 16 months after rTMS sessions, with an initial gain over 3 months after the last rTMS cure session. Furthermore, after the failure of one antidepressant treatment, rTMS would be less expensive and would allow a better quality of life and greater function compared to conventional treatment strategies [62]. Although the rTMS is less effective than ECT [32], it is better tolerated and does not require general anesthesia with curarization [48, 63], with a compliance rate of 97% versus approximately 50% for medication. Its mechanisms of action are manifold: improvement in prefrontal metabolism [64], neuromodulation of remote cerebral areas and regulation of the hypothalamo-hypophyseal axis [65]; modulation of cortical excitability [66, 67]; and synaptic plasticity and dopaminergic secretion [68, 69]. However, long-lasting efficacy rTMS is limited to approximately 3–6 months after the curative therapy [70]. It is important to note that a patient who respond to an initial rTMS cure has an 80% chance of responding to another rTMS cure [29], hence the need to evaluate this impact on the prognostic and economic modification.

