According to health economic criteria, several parameters are necessary to calculate the numbers of individuals in a health economic study including [73]: cost and QALY average deviation over time; costs and QALY standard deviation in each arm; correlation between the costs and QALY difference; and the QALY value. These data are ideally obtained from the literature or a pilot study. However, no source data were available for our study concerning the costs and the quality of life in depression. Moreover, there is no official recommendation available on the QALY monetary value in France [56]. That is why we preferred to calculate the number of individuals required according a clinical criterion, the rate of response at 12 months, rather than a risky health economic hypothesis. This rate of response after the rTMS cure is estimated at 60% in arms A and B, based on the same rTMS protocol already used in French context in that population [48]. According to the literature, we adopted a hypothesis of 30% of sustained response at 1 year in arm A [23, 31, 49, 50] and in arm B [23, 49, 51, 52], and n hypothesis of 11% rate of response sustained at 1 year in arm C [53]. Assuming a 5% (bilateral) type I error, a power of 80%, and an attrition rate of 80%, a total of 318 individuals is required, with 106 in each arm.

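### The stated sample-size inputs, including 80% attrition, do not give 106 per arm; correcting attrition to 20% is not enough, and the calculation behind 318 needs restating.

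*Protocol article*

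**What the plan says.** The Statistical analysis section of the protocol article explains that no cost or quality-of-life data were available for a health-economic calculation, so the trial is sized on sustained response (a MADRS decrease of more than 50%). For the active arms, "we hypothesized a rate of 30% maintained response at 1 year for arm A", with the same rate for arm B and 11% for arm C. It then states: "Assuming a 5% (bilateral) type I error, a power of 80%, and an attrition rate of 80%, a total of 318 individuals is required". On multiplicity it says only that "only two comparisons will be carried out: arm A versus arm C, and arm B versus arm C".

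The Discussion gives the calculation a second time with the same error rate, power and attrition: "a power of 80%, and an attrition rate of 80%, a total of 318 individuals is required, with 106 in each arm". It also reports the treatment-as-usual study cited for the arm C rate: "They showed a response rate of 11.6% at 12 months and 18.4% at 24 months".

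Under Randomization the ratio is 1:1:0.5:0.5 for A, B, C1 and C2, so arms A, B and C are of equal size, and 3 × 106 = 318.

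**The concern.** An attrition rate of 80% is implausible as a planning value and, taken literally, is incompatible with 80% power at this trial size. Because it appears in two sections, a reader cannot treat it as a single slip. Sustained response is the only quantitative basis for 318, so if this calculation cannot be followed, nothing else in the article supports the trial's size.

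Two practical matters depend on it. First, the planned attrition is the benchmark against which actual loss to follow-up will be judged, and 80% would make almost any loss look expected. Second, if changing 80% to 20% does not recover 106, then the per-comparison error rate, the control rate, the test or the power differs from what is printed, and the reader cannot tell which.

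**Working it through.** **Inputs.** p₁ = 0.30, p₂ = 0.11, two-sided α = 0.05 (z = 1.960), power 0.80 (z = 0.842), attrition d = 0.80, result 106 per arm (all from Statistical analysis and Discussion). Equal arms (Randomization). As a sensitivity value, p₂ = 0.116 (Discussion).

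**Step 1. Evaluable patients per arm.** Pooled two-proportion formula, with Δ = 0.19 and mean p = 0.205:

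n = [z(α/2)·√(2·0.205·0.795) + z(β)·√(0.30·0.70 + 0.11·0.89)]² / Δ²

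= [1.960 × 0.5709 + 0.842 × 0.5549]² / 0.0361 = (1.119 + 0.467)² / 0.0361 = 69.7, so 70.

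Other standard methods give 67 (unpooled), 68 (arcsine), 78 (Fisher exact) and 80 (continuity-corrected).

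**Step 2. The plan's own figure, with 80% attrition as printed.** n/(1 − d): 70/0.2 = 350 per arm (1,050 in total); 80/0.2 = 400 per arm (1,200 in total). The cruder inflation n(1 + d) gives 67 × 1.8 = 121 up to 80 × 1.8 = 144. No variant gives 106.

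**Step 3. In reverse.** 106 × 0.2 = 21.2 evaluable per arm. Power = Φ[(√21.2 × 0.19 − 1.119)/0.5549] = Φ(−0.44) = 0.33.

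**Step 4. Replace 80% by 20% and keep everything else.** 70/0.8 = 87.5, so 88 per arm (264 in total). With continuity correction, 80/0.8 = 100 per arm (300 in total). Neither is 106. From the other direction, 106 × 0.8 = 84.8 evaluable gives power Φ[(√84.8 × 0.19 − 1.119)/0.5549] = Φ(1.137) = 0.87 at 5%, not 0.80.

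**Step 5. Which inputs do reach about 106?**

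| Control rate | α per comparison | Test | Attrition | Evaluable per arm | Randomised per arm |
|---|---|---|---|---|---|
| 11% | 2.5% | pooled, uncorrected | 20% | 84.5 | 84.5/0.8 = 105.6 |
| 11.6% | 5% | continuity-corrected | 20% | 86 | 86/0.8 = 107.5 |
| 11.6% | 5% | Fisher exact | 20% | 84 (power 80.2%) | 84/0.8 = 105 |
| 11% | 5% | continuity-corrected | 25% | 80 | 80/0.75 = 106.7 |
| 11% | 2.5% | continuity-corrected | 10% | 95 | 95/0.9 = 105.6 |

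For the first row, n = (2.241 × 0.5709 + 0.467)² / 0.0361 = 84.5. Each row changes the printed attrition and at least one other printed or unstated input.

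**The case against.** The fairest defence is that 80% is a slip for 80% retained. On that reading about 85 evaluable patients per arm give about 87% power at the stated 5% (uncorrected pooled test), so the trial is not undersized for response. The 33% power and the 1,050 patients then describe a trial that nobody planned. This stands as to consequence. It does not rescue the statement, because Step 4 shows that the corrected sentence still does not produce 106.

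A reader might go further and infer that 106 can only come from splitting 5% into 2.5% for A–C and 2.5% for B–C, and that the analysis then abandons this protection. The split is a plausible explanation: it keeps the printed response rates, and the remark about two comparisons stands beside the calculation. But the documents do not establish it:

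- The article states 5% and mentions no split.
- The second and third rows of the table reach 105 to 108 at 5% per comparison, using the rate the Discussion itself reports for the cited study.
- The split reproduces 106 only with some tests. By Fisher's exact test, 85 per arm at 2.5% has about 76% power.
- The 95% confidence intervals in the Statistical analysis section are stated for costs, QALYs and the ICER, for remission, and for rating-scale scores. None is stated for sustained response, so they do not show that a sizing alpha was dropped. The level used for each comparison may also be set in an analysis plan that is not shown.

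Nor does the Background figure, "an average rate of 3% for dropouts", settle the planned attrition. It describes adherence to rTMS in the literature, not completeness of 12-month follow-up.

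**Conclusion.** The sample-size statement is wrong as written, in both places. The printed inputs need about 70 to 80 evaluable patients per arm, or about 350 to 400 randomised at 80% attrition, against the stated 106. Taken literally, the trial would have about 33% power.

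That 20% attrition was meant is likely but is an inference. Even then, the stated 5% and 30% versus 11% lead to 88 per arm (100 with continuity correction), so at least one further input is misstated or missing. Several incompatible designs fit 106, and the article does not identify which applies. A hidden correction for two comparisons is one candidate and no more.

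The finding concerns sustained response, the criterion used for sizing. It says nothing about precision for the ICER, for which the article makes no calculation.

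**What to change.** In both the Statistical analysis section and the Discussion, correct the attrition figure (to 20%, if that was meant). In the same sentence, state the per-comparison alpha, the arm C rate, the test, the evaluable number per arm and the resulting power that produced 106. These should come from the original calculation and not be inferred from the total.

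- If 5% per comparison, 30% versus 11% and 20% attrition were meant, restate power as about 87% (uncorrected pooled test, 85 evaluable per arm).
- If alpha was split, say so, and test 12-month sustained response for A–C and B–C at 2.5% each.
- If the 11.6% rate or a continuity-corrected or exact test was used, print that instead.

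The cost is wording in two places. No additional patients are needed if 20% attrition was meant. If a larger loss was really planned, the size must be recalculated.

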## Background

Depression is a debilitating difficult-to-treat disease associated with enormous costs for our society. According to the Global Burden Study in 2010, it is a leading cause of morbidity and disability worldwide, thus a public-health priority calling for cost-effective interventions [1]. Affecting the whole lives 24% of French people [2], the direct and indirect yearly cost for depression is estimated at 14 billion Euros in France [3]. These expenditures include co-morbidities such as substance abuse, suicide attempts and suicide achieved, somatic multi-morbidities, loss of production, working stoppages, the increased use of the healthcare system (hospitalization, etc.), the impact on the quality of life and its socio-professional aftermath [3–5]. Despite appropriate treatment, 40% of patients do not respond to initial antidepressant treatment and 20% present with a chronic form of depression (> 2 years despite standard treatment administered correctly) [6]. Typically, treatment-resistant depression (TRD) refers to an absence of remission after at least two different antidepressant lines at an effective dosage over a period of 6 weeks during the current episode. Indeed, 30%–40% of patients with major depression hold disabling symptoms after several antidepressant treatments [7–9]. Even in the cases of initial remission, the study of reference for pharmacotherapy, STAR*D, shows a 43% rate of relapse at 1 year [7, 10]. The economic cost of depression is much higher in the case of TRD [11, 12] and is associated to the higher rate of medication non-observance at around 63% [5]. Depression after two antidepressant agents increases the cost of care by 40%–100% in comparison with non-TRD [13]. Moreover, in 2000, a meta-analysis of Dimatteo et al. [14] demonstrated that the non-observance rate of non-psychiatric treatments is three time higher among patients with anxio-depressive syndrome increasing its global burden. Care for depression is therefore a challenge with important direct and indirect costs in the short and long term, especially in its treatment-resistant form.

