### Assessments

The following variables are documented during the baseline visit: sociodemographic (date of birth, age, gender, laterality, professional and marital status); medical history (length of illness, duration of the current episode, co-morbidities (psychiatric, addictive, somatic); and current treatment degree of prior therapeutic resistance according to the Maudsley Staging Model (MSM) [37]).

The following variables are regularly evaluated from the beginning to the end of the study, as shown in Table 1: intensity of the depression according to the MADRS [35]; the Beck Depression Inventory 13 items (BDI 13) [38]; the Clinical Global Impression - Severity (CGI-S) [39]; QALY evaluation by the Euroqol Five Dimensions Questionnaire (EQ-5D) [40]; the quality of life with the Short-Form 36 Health Survey (SF-36) [41]; the drug compliance according the Medication Adherence Rating Scale (MARS) [42] and the Compliance Rating Scale (CRS) [43, 44]; and pharmacological and non-pharmacological treatments statement with the eCRF. The response will be defined by a 50% reduction of MADRS, and remission by MADRS score of < 8. All significant side effects or adverse events will be reported in the eCRF by the research team.

**Table 1 Tab1:** Hospital production costs in France for a rTMS session

Medical	
Medical time	€39 (US$43.26)
Nurse time	€32 (US$35.50)
Equipment	€33.57 (US$37.24)
Structural expenses	€23.11 (US$25.64)
Total	€127.68 (US$141.64)

Potential explanatory variables to evaluate the depression economic cost are: formal and informal cares consumption (eCRF questionnaire); depression’s socio-professional aftermath with the Work Productivity and Activity Impairment (WPAI) [45] and eCRF questionnaire; health economic analysis with micro-costing; and data extracted from the National Health System Database of Health (NHSD) with the French hospital expenditure database (E.U. Program of Medicalization of Information Systems [PMSI]). Data from the NHSD include: medical consultations; hospitalizations; pharmacological treatments; work stoppages; daily allowances; care-related transports; imagery and biology; nursing cares; and losses of production in association with the WPAI.

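### The incremental cost in the primary ICER is written as a raw difference between arms; prespecified adjustment for baseline variables already recorded would gain some precision at almost no cost

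*Protocol article*

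**What the plan says.** All references are to the protocol article.

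- **Cost comparison (Statistical analysis).** By arm, "resources consumed, including costs and QALY, will be presented with average and dispersion for each group". Then: "The comparison between cost, QALY, and the years of life gained in each arm, including ICER analysis, will be evaluated with the estimation" of standard deviations and "corresponding 95% confidence intervals (CI) following the non-parametric bootstrap method". No regression model or covariate is named for cost.
- **Numerator (Statistical analysis).** By way of example, "the ICER between arms A and C will be calculated as follows": cost in A minus cost in C, over QALYs in A minus QALYs in C. The cost terms are defined simply as the depression costs of each arm.
- **Baseline adjustment (Statistical analysis).** "If there is a baseline deviation between arms of the study about the quality of life estimated with the EQ-5D, two analyses will be conducted". Raw scores are used in the first and adjusted scores in the second. This covers quality of life only, and only if a deviation is seen.
- **Sensitivity analysis (Statistical analysis).** The one described varies the cost and pricing of rTMS sessions.
- **Baseline data (Assessments).** Maudsley stage, duration of the current episode and professional status are recorded at the baseline visit. MADRS is rated from the start of the study.
- **Balance (Randomization).** Permuted blocks by center, with no stratification or minimisation on patient factors.
- **Database link (Statistical analysis).** To cost depression, "clinical data matching the eCRF and the NHSD will be applied using the patient identification number".

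**The concern.** The plan treats baseline imbalance as worth handling in the denominator of the ICER and not in the numerator. Cost is the side where precision is least under control, because the trial was sized on sustained response: the Statistical analysis and Discussion sections say that no cost data were available for a calculation. The indirect costs include lost production (Discussion), so employment status at entry is a plausible predictor of cost. Current episodes may have lasted from 12 weeks to 3 years (Inclusion criteria), so the patients differ in chronicity.

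If such variables predict 12-month cost at all, leaving them out makes the interval for incremental cost wider than it need be. Adding them after the data are seen would be open to challenge, so the choice belongs in the plan.

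**Working it through.** **The plan's own figure.** The article gives no precision target for cost, so there is none to reproduce. Its 106 per arm comes from response rates of 30% and 11%. I used n = [z(1−α/2)·√(2p̄(1−p̄)) + z(0.80)·√(p₁q₁ + p₂q₂)]² / (p₁ − p₂)², with p̄ = 0.205.

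- α = 0.05 gives 70 per arm, and 70/0.8 = 87.5, so 88 (264 in total).
- α = 0.025 gives 85 per arm, and 85/0.8 = 106.25.

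The printed 106 is therefore approached only if the stated 80% attrition means 80% retention and α is split over the two comparisons. That is a separate matter. It is used here only to choose two sample sizes: 106 randomised and, as an assumption, 85 analysed per arm.

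**Precision of the cost difference.** The allocation makes A:C and B:C both 1:1. In units of the cost SD:

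- unadjusted SE = √(2/n)
- adjusted SE = √((1 − R²)·2/n), where R² is the share of cost variance explained by the baseline covariates
- 95% half-width = 1.96 × SE
- equivalent unadjusted sample = n/(1 − R²)

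At n = 106 the unadjusted half-width is 1.96 × √(2/106) = 1.96 × 0.1374 = 0.269 SD. At n = 85 it is 1.96 × 0.1534 = 0.301 SD. The documents give no R², so a range is shown:

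| R² (assumed) | SE ratio | Half-width, 106 per arm | Equivalent n for 106 | Half-width, 85 per arm |
|---|---|---|---|---|
| 0 | 1.000 | 0.269 | 106 | 0.301 |
| 0.05 | 0.975 | 0.262 | 111.6 | 0.293 |
| 0.10 | 0.949 | 0.255 | 117.8 | 0.285 |
| 0.20 | 0.894 | 0.241 | 132.5 | 0.269 |

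**Check with skewed costs.** In a simulation with gamma-distributed costs and one baseline predictor (85 per arm, 4,000 runs), both estimators were centred on the true difference. The adjusted-to-unadjusted SE ratios were 1.00, 0.95 and 0.90 at R² 0, 0.10 and 0.20, in line with √(1 − R²).

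**Chance imbalance is the same variance.** At 106 per arm and R² 0.20, the unadjusted variance 2/106 = 0.0189 splits into 0.0038 due to covariate imbalance (SD 0.061) and 0.0151 from the rest. The unadjusted interval already contains both parts. Adjustment removes the first.

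**The case against.** The strongest case against is that the article is silent rather than wrong. The ICER formula is the textbook definition, given as an example; nothing in it rules out adjusted means; and the covariates of a cost model are ordinary content for an analysis plan that is not shown. This stands in part, and it is why the point is an improvement and not an error. But the article does take up baseline adjustment in the economic analysis and names EQ-5D alone. Assessments has a list of potential explanatory variables for cost, but these are largely components of cost, and no model is said to use them.

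Four stronger readings are tempting, and the documents do not support them:

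- **Bias.** A reader might infer that the raw difference is biased by imbalance. Randomisation makes it unbiased, and its interval already allows for chance imbalance.
- **Strong prediction by resistance.** The Background says: "Depression after two antidepressant agents increases the cost of care by 40%–100% in comparison with non-TRD". That contrasts resistant with non-resistant depression. Every participant here is treatment-resistant, so the figure does not show how well Maudsley stage predicts cost within this sample.
- **A large power gain.** Assuming a correlation of 0.5 between prior and follow-up cost would turn 80% power into about 90%. No section provides for extracting cost from before randomisation, and no hypothesis test on cost is planned.
- **A reversed dominance conclusion.** This would need the cost and QALY variances and their correlation, none of which is given.

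**Conclusion.** The point holds as a matter of efficiency. As written, the incremental cost is an unadjusted difference, baseline adjustment is confined to EQ-5D, and usable baseline variables that the randomisation does not balance are left out. The estimate is valid but probably less precise than it could be.

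The gain is modest and rests on an assumed R². At 106 per arm the interval for incremental cost narrows by about 2.5%, 5% or 11% at R² 0.05, 0.10 or 0.20, and not at all at R² 0. These figures concern the cost difference alone. The effect on the ICER interval also depends on the QALY side and cannot be worked out from the article.

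**What to change.** State in the analysis section that, whatever imbalance is observed:

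1. In each bootstrap replicate and each imputed data set, the A–C and B–C cost differences are estimated by regression of 12-month cost on arm plus Maudsley stage, duration of the current episode, professional status and baseline MADRS.
2. Each patient's cost and QALY stay paired, for example through a joint model, so that their correlation is preserved.
3. The adjusted cost difference is the ICER numerator, and the raw difference is reported as a sensitivity analysis.

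Add NHSD cost from before randomisation only if the extraction already reaches back that far. In the same edit, reconcile the patient-level NHSD link in Statistical analysis with the Discussion, which describes the NHSD data as coming from a matched population.

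The cost is a few lines of text and slightly more programming. The four covariates need no new data collection.
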